## 2. Glossary

*<Please insert any abbreviations and key terms>*

## 4. Summary and synopsis

|                                                             |                                                                                                                                                                                                                                                                                                                                                                                                                                                                                                                                                                                                                                                                                                                                                                                         |
|-------------------------------------------------------------|-----------------------------------------------------------------------------------------------------------------------------------------------------------------------------------------------------------------------------------------------------------------------------------------------------------------------------------------------------------------------------------------------------------------------------------------------------------------------------------------------------------------------------------------------------------------------------------------------------------------------------------------------------------------------------------------------------------------------------------------------------------------------------------------|
| Short title                                          | Working in the hot zone study                                                                                                                                                                                                                                                                                                                                                                                                                                                                                                                                                                                                                                                                                                                                                           |
| Methodology                                          | Qualitative: interviews and focus groups only                                                                                                                                                                                                                                                                                                                                                                                                                                                                                                                                                                                                                                                                                                                                           |
| Objectives / aims                                    | To understand the acceptability and feasibility of delivering life-saving interventions in a terror-attack situation, from the perspective of pre-hospital providers and the public.                                                                                                                                                                                                                                                                                                                                                                                                                                                                                                                                                                                                    |
| Number of participants                               | Professional: up to 30 pre-hospital healthcare workers, police and firefighters
Public: up to 32 members of the public                                                                                                                                                                                                                                                                                                                                                                                                                                                                                                                                                                                                                                                               |
| Inclusion and exclusion criteria                     | 
Inclusion criteria:
 
Maximum variation sample to include:
 
 
1. Paramedics, Pre-hospital Physicians, Police Officers, and Firefighters) in London and Manchester. Sampling will ensure an adequate variation in age, gender, years of professional experience, lived experience of working during a terrorist attack and seniority (to include both a range of ranks of frontline professionals and senior operational leaders).
 
2. People with lived experience of being involved in such an attack in London or Manchester.
 
 
Exclusion criteria:
 
 
• Unwilling or unable to give consent
 
• Inability to understand written and/ or verbal English
 
 |
| Statistical methodology analysis and (if applicable) | Inductive analysis using thematic and comparative analysis of interview and focus group transcripts                                                                                                                                                                                                                                                                                                                                                                                                                                                                                                                                                                                                                                                                                     |
| Study duration                                       | 12 months                                                                                                                                                                                                                                                                                                                                                                                                                                                                                                                                                                                                                                                                                                                                                                               |

## 5. Introduction

During the initial phase of terrorist events, a 'hot zone' is created where there may be on-going terrorist activities with active threats to life. Current policy is that emergency medical services are not allowed into the hot zone until it has been cleared, a process which may take hours. This is especially likely in marauding attacks, where there are multiple terrorists moving from location to location, such as in recent attacks in London and Paris, and active shooter events in the USA. The vast majority of deaths in these events occur at scene, before emergency services are allowed in the hot zone. Autopsy evidence from mass shootings in the US suggests that some patients die from potentially survivable injuries that may have been treated at scene [Smith et al, 2019]. If these findings are consistent across other types of events and healthcare systems, providing trauma care in the hot zone could dramatically reduce deaths in terrorist events.

However, to send emergency personnel into an area where there is an active terrorist threat to their own life is clearly a major decision. Potential gains from hot zone deployment must greatly offset the associated risks. Key information on which to make this decision does not currently exist, namely: (A) what proportion of prehospital terrorist deaths are potentially preventable; (B) What interventions would be required to prevent these; (C) how quickly these would need to be delivered; (D) who can deliver these interventions. Furthermore, it is important to understand whether frontline and command staff would perceive that therapeutic gains from hot zone deployment would justify the potential risks. These factors will vary depending on the nature and scale of each event and need to be synthesized into a system-level view of these events to allow balanced evidence-led decisions.

The potentially preventable causes of death in a terrorist attack depend on the mechanism. Available literature is predominantly military in origin, with haemorrhage as the leading cause in 90.9% of cases, and 8% associated with airway compromise.[Eastridge et al, 2012] Emerging civilian data has looked at causes of death in US active shooter events, where lung injury, was the most common cause of potentially preventable death. More data is required, but skills to manage pneumothoraces and ventilatory failure may be required forward of the cold zone where it is currently provided in the UK [<https://www.jesip.org.uk/doctrine>].

New Joint Operating Procedures that came into place this year now allow healthcare resources to operate forward of the cold zone, however training and operating procedures are yet to be developed to evolve the current response to allow this to occur, and there may be barriers to commanders and responders being willing to do so which are extremely important to explore.

The timing of interventions is also critical if they are to have the potential to save life. Minimal data is available on exact timings of deterioration and intervention. Although dated, the most detailed database available is that of the Wound and Data Munitions Effectiveness Team (WDMET). This is meticulously collected data from 7,801 American casualties from Vietnam, documenting all causes, injuries, timings and interventions. In order to address the preventable deaths amongst the 42% that die in

Working in the Hot-zone study v1.1 040621

the first 30 minutes (26% in 5 minutes and 16% in 5 to 30 minutes) [Carey, 1987], the interventions need to be performed by those who can rapidly access the casualties.

During the 2017 London Bridge terror attack, some casualties in the hot zone could not be accessed by the ambulance service for more than 3 hours due to them being designated a 'hot zone'. These casualties were managed by police during this time. In his Regulation 28 report on action to prevent future deaths [Lucraft, 2019], the Chief Coroner noted that systems and practices should be examined to address the problem that hot and warm zones pose - that they could be designated for long periods of time, whole areas could be considered out of bounds for ambulance staff, and there is risk of delay in getting medical help to casualties.

Practice varies internationally, and in the 2015 Bataclan siege in Paris, two RAID doctors entered with police cover and triaged all (approximately 100) casualties from the orchestra pit while the intervention plan was co-ordinated [Crit care, 2016: 20(37)]. All of the live casualties were evacuated within 30 mins of RAID entering the theatre, and 30 mins before the terrorists were neutralised. Had the evacuation waited until after the police intervention, as in the UK, it would also have been 3 hours before any medical care was delivered. Only 1.4% of casualties evacuated from the Bataclan later succumbed to their injuries in contrast to approximately 10% in historical data, although the prehospital death rate remained high [Langlois & Ploquin, 2016].

This qualitative study presented for your review is part of a larger, NIHR funded, multimodal study to fill the identified evidence gap. The overall study will establish critical information on prehospital deaths and life changing injuries in terrorist events, their preventability, time course of deterioration and which therapeutic interventions would be required.

This qualitative study has been designed to explore the potential impact of hot zone working on different prehospital providers, from a range of perspectives, and the potential feasibility and acceptability of delivering therapeutic interventions in the hot zone to reduce overall mortality of future events.

## **6. Study objectives**

### **6.1. Primary objective**

To understand the acceptability and feasibility of delivering life-saving interventions in the hot-zone (unsafe zone) during a terror-attack situation, from the perspectives of emergency healthcare workers, other frontline professionals (fire and police) and the public.

Study Question 1:

What are the perspectives and views of emergency healthcare workers, other frontline professionals (fire and police), senior operational leaders and the public about pre-hospital providers working in a terrorist attack situation?

## Study Question 2:

What interventions would emergency healthcare workers, other frontline professionals (fire and police) and operational leaders consider as potentially acceptable and feasible to deliver in a terrorist attack situation ?

## 7. Study population

We will recruit participants with lived experience of terror attacks in the UK. There are two specific groups we wish to recruit:

1. Healthcare professionals and other frontline workers, who have worked during such an event. N.B. With these participants we are seeking to understand their personal experience and views, rather than a representation of their employers views.
2. Members of the public who have been involved in such an event or potentially the relatives of those who have died during such an event.

We will purposively sample interview participants from two UK cities (London and Manchester) that have been the target for multiple terrorist attacks to provide variation of context. We will use different methods to recruit these participants.

### **Health professional and other frontline workers**

We will recruit a maximum-variation, purposive sample of up to 30 interview participants, from the four main professional groups involved in providing a response to terrorist attacks (Paramedics, Pre-hospital Physicians, Police Officers, and Firefighters), across the two cities. Sampling will ensure an adequate variation in age, gender, years of professional experience, lived experience of working during a terrorist attack and seniority (to include both a range of ranks of frontline professionals and senior operational leaders).

Given the purposive sample and relatively small number of participants who meet our criteria we will use our research group professional networks and a snowball sampling approach. In this approach, contacts well known to the research group will be invited (by email) to be participants (with the ability to decline as per any research study). Following this, we will discuss our sampling requirements with these participants (referred to as 'seeds' in the literature) and ask if they know of any suitable colleagues who they could pass the invitation on to. We will continue to recruit using this approach until theoretical saturation is achieved (see also Data Analysis section below).

To protect potential participants from any coercion to join (e.g. by a manager or senior colleague) we will take the following steps:

1. We will only require 2-3 operational leaders to be participants. We will approach these directly using the professional networks of our group. Moreover, we will NOT ask these participants to act as seeds for further participants thus preventing any senior leader coercion.
2. For frontline professionals (paramedics, physicians, police and fire) we will a) impress upon the initial seeds the importance of the voluntary nature of recruitment and discuss with them who they may ask to participate, who and

why and b) as with any study, on initial contact with new potential participants we will give people clear opportunities to consider participation and ensure they understand they do not need to participate and can withdraw consent at any time prior to publication.

### **Members of the public with lived experience of terror attacks**

We will advertise the opportunity to be a participant in this study through two known terror survivor groups with which our study group has contact. These groups are: The Survivors against Terror Group (<https://survivorsagainstterror.org.uk>) and the Counter Terrorist Association Network which has links to a group of survivors as well.

The invitation to participate and the Participant Information Sheet (PIS) will be sent by email by our contact in the group (who is either a family liaison officer or psychologist). These contacts will carefully consider who to invite, based upon knowledge of these groups and will approach the matter sensitively. Those who reply to this expressing interest will be given the opportunity to ask further questions before agreeing or declining to participate.

### **7.1. Inclusion criteria**

Maximum variation sample to include:

- Paramedics, Pre-hospital Physicians, Police Officers, and Firefighters) in London and Manchester. Sampling will ensure an adequate variation in age, gender, years of professional experience, lived experience of working during a terrorist attack and seniority (to include both a range of ranks of frontline professionals and senior operational leaders).
- People with lived experience of being involved in such an attack in London or Manchester.

### **7.2. Exclusion criteria**

- Unwilling or unable to give consent
- Inability to understand written and/ or verbal English

## **8. Study design**

Qualitative study design.

### **Health professional and other frontline workers**

Semi-structured interviews will be conducted by the Principal Investigator (TS) by telephone / online using Zoom.

The interviews will start with narrative approach to encourage participants to relate their experiences and perceptions about working during a terrorist attack (in cold, warm or hot-zones) in depth. Following this, more structured enquires will prompt discussion on the acceptability and feasibility of delivering specific healthcare interventions in a hot-zone environment. These to include: (1) an exploration of the participants willingness, or otherwise, to enter the hot-zone during a future terrorist attack, or (2) to allow teams to enter if in a command role, and the participants feelings

and perceptions that shape this; (3) mitigating factors that may affect the participants willingness to enter the hot zone, and (4) strategies that could reduce perceived barriers to allow teams to enter. Interviews will be approximately 45-60 minutes in duration, will be audio recorded (with consent) and transcribed. Recruitment to interviews will continue until theoretical saturation is reached (maximum 30).

### **Members of the public with lived experience of terror attacks**

Focus groups will be conducted by the Principal Investigator (TS) online using Zoom. The interviews will start with narrative approach to encourage participants to relate their experiences and perceptions of the event they were involved in. Following this, the concept of health workers and frontline workers delivering healthcare interventions will be explored. Focus groups will be approximately 60 minutes in duration, will be audio recorded (with consent) and transcribed. Recruitment will continue until theoretical saturation is reached (maximum 4 groups, 32 participants).

For both data sources, analysis will follow an inductive approach, with thematic and comparative analysis used to identify and develop key themes emerging from this rich dataset. Analysis will start after the 3rd interview and then continue concurrently with data collection. Data analysis will be led by the PI (TS) with regular data meetings convened with the study management team and PPI committee, to review and comment on findings. Analysis will use the software Nvivo (v.11) to collate and organise the data.

## **9. Ethics**

Ethical approval is being sought from QMUL REC.

As this is a non-interventional qualitative study, it is low-risk in most respects but we are alive to the fact that the topic may be sensitive for potential participants.

The following risks, burdens and benefits are possible:

- Risks and burdens: participants may become distressed through the recounting of their experiences, either during the research activity or subsequently
- Benefits: participants are contributing to research that will have the potential to save the lives of people in the event of any future terror attacks and so are contributing something important to society by sharing their experiences and perceptions.

We address this sensitivity, and the risks and burdens, in the following ways:

1. Recruitment is through professional networks or through email advert and so there is no direct contact with the research team unless the potential participant makes contact
2. Once contact has been made, a PIS will be shared by a method of their choice (email or post) and then, again, the potential participant will be free to contact us if willing to participate or not if they do not wish to. We will send one single follow up to those who have expressed an interest but have not responded further. After this, no further contact will be made from the research team
3. Informed consent will be obtained for each participant and participants will be clearly made aware that they are free to cease participation at any time.

4. The interviews and focus groups will be led by the PI who is an experienced clinician and qualitative researcher, who will remain aware throughout of the need for sensitivity and look for any signs of participant distress
5. If any participant does show signs of distress the interview or focus group will be paused and the participant invited to either cease completely or temporarily their participation
6. For healthcare workers and other frontline professionals relevant support services will be signposted at the end of each interview.
7. For members of the public we will ensure that they have access to a support group including a clinical psychologist who already provides support to the groups from which we are recruiting .
8. All participants can be assured of anonymity and no identifying details will be used in any publications or other public forums (e.g. conferences).

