## 11. Data handling and record keeping

### 11.1. Data management

**Data storage:** Data collection and storage will follow the Barts Health / QMUL data protection policy (e.g. records of personal details (names, addresses, telephone numbers) kept in a secure place and separately from research records). All data will de-identified with raw data stored on a non-networked, password protected laptop along with a 'key' (i.e. a list of ID numbers and names) which connects the identifiable and de-identified data. Potentially identifiable material will not be used in published or publicly accessible outputs unless express written consent has been given (e.g. permission to use direct quotes will be sought.)

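### Section 9 assures every participant of anonymity, which shared focus groups cannot provide, and section 11.1 stores the name key with the raw data despite its own rule to keep names apart

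*Protocol*

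**What the plan says.** **The promise.** Section 9 (Ethics) lists eight measures that answer the sensitivity of the topic and the risks to participants. Item 8 reads: "All participants can be assured of anonymity and no identifying details will be used in any publications", and extends its second clause to other public settings such as conferences.

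**Who hears or knows what.** Under section 8, members of the public take part in online focus groups led by the principal investigator, with a ceiling of "maximum 4 groups, 32 participants". Section 7 says they are reached through two survivor groups, by a contact inside the group: "These contacts will carefully consider who to invite, based upon knowledge of these groups". Professionals are interviewed one at a time. Section 7 recruits them from the team's own contacts and then by snowballing, in which early participants pass the invitation to colleagues after discussing with the team whom they might ask. On senior staff, section 7 says: "We will only require 2-3 operational leaders to be participants". Leaders are approached directly and do not recruit others.

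**Data storage.** Section 11.1 says names and contact details are "kept in a secure place and separately from research records". The next sentence has "raw data stored on a non-networked, password protected laptop along with a 'key", and explains the key as the list that ties ID numbers to names. The same section bars potentially identifiable material from public outputs "unless express written consent has been given", with permission for direct quotes as its example. Section 11.2 names recordings and transcripts as the source data. Section 11.3 says recordings carry only a participant or site number, data are reported anonymously, and quotes are used with permission and without direct attribution.

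**The concern.** Two safeguards offered to participants do not work as written.

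The first is the promise itself. Anonymity means that nobody can connect a person with what that person said. In a focus group every other member can. Survivors, and possibly bereaved relatives, would agree to describe a traumatic event on the strength of an assurance that fails as soon as the group meets. Section 9 names distress as the possible harm and does not mention disclosure by another member. Consent given on an overstated promise is less informed than it should be.

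The second is the coding of the data. Numbering the recordings protects participants only while the list that decodes the numbers is held elsewhere. If both sit on one device, anyone who gains access to it has the accounts and the names together, which is what the separation rule is there to prevent.

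**Working it through.** The plan gives no statistical figure on this point, so the check is a comparison of its sections with a little arithmetic.

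**1. Focus groups (firm).**
- Inputs, section 8: at most 4 groups and 32 people.
- Average size of a full group: 32 / 4 = 8. Other members who hear each account: 8 - 1 = 7.
- The protocol fixes no size for a single group, so 8 is the average when both ceilings are reached. The conclusion does not depend on it, because any group of two or more discloses each account to someone outside the team.
- Item 8 covers all participants and so includes these 32. Sections 7, 8, 9 and 11 contain no rule on confidentiality between members and no statement that the promise is limited in groups.

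**2. Snowballed professionals (not guaranteed).**
- The seed knows who was sent an invitation.
- Under section 9, items 1 and 2, the invitee then decides whether to contact the team. Nothing in the protocol tells the seed who took part or what was said.
- Participation may be guessed but is not disclosed by design.

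**3. Operational leaders (not guaranteed).**
- Section 7 needs 2-3 leaders among at most 30 professional interviewees, so at most 3 / 30 = 10%.
- The same section describes the pool of people who meet the study's criteria as fairly small. The size of the pool of leaders is not given, so the chance of recognition cannot be calculated.

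**4. Key and raw data (firm).**

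| Section | What it requires or does |
|---|---|
| 11.1, first sentence | Names and contact details held apart from research records |
| 11.1, next sentence | List of ID numbers and names held on the laptop with the raw data |
| 11.2 | Source data are recordings and transcripts |
| 11.3 | Recordings identified by number only |

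The recordings are raw data and research records, and the number is their protection. The second row places the decoding list beside them, which conflicts with the first row. If everyone is listed, the key holds up to 30 + 32 = 62 names.

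**5. Item 8 against the consent wording (minor).** Item 8 says flatly that no identifying details will be used. Section 11.1 allows potentially identifiable material with written consent. Unattributed quotes used with permission, as in section 11.3, fit both statements. What remains is an absolute statement beside a conditional one.

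**The case against.** The best reply is that item 8 concerns outputs. Its second clause speaks of publications and conferences, and section 11.3 explains anonymity as numbered recordings, anonymous reporting and unattributed quotes. On that reading focus groups do not break the promise. The reply has force as to intent, and it makes the repair mainly one of wording. It does not remove the point: the first clause is not limited to outputs, it stands among the protections against participant risk, and a participant would read it broadly. Nor does it supply a rule between members.

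On the key, one can argue that the laptop holds identifiable raw material while de-identified records are kept elsewhere. Section 11.3 weakens this, since the recordings are themselves coded by number. The laptop is offline and password protected, which lowers the risk without meeting the separation rule.

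It is also fair to say that the information sheet is not shown and may state limits or ground rules, and that members drawn from existing survivor groups may already know one another.

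Several stronger readings are tempting, and the documents do not support them:
- **Anonymity is impossible for every participant.** This holds for focus-group members only. For professionals it is a question of what can be guaranteed.
- **Leaders can be picked out by role and city.** No section says that quotes will carry such labels.
- **Sections 9 and 11.1 flatly contradict each other on identifiable material.** They are largely compatible, as shown above.
- **Professionals' jobs are put at risk, or they will give institutional answers.** Professionals are interviewed singly, so the focus-group failure does not reach them, and an effect on candour is conjecture.
- **Any failure of the laptop exposes 62 people.** Failure loses data. Only access to the contents would expose names, and 62 is the ceiling on the list, not an estimate of harm.

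**Conclusion.** The point holds on two limbs. Item 8 makes an unqualified promise that cannot be kept for up to 32 focus-group participants, each heard by about 7 others in a full group, with no stated limit or member rule. Section 11.1 sets a separation rule and departs from it in the next sentence, for a key that may list up to 62 people. For snowballed professionals and the 2-3 leaders, the most that can be said is that anonymity cannot be guaranteed.

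This rests on reading the first clause of item 8 as it stands and on treating numbered recordings as research records. Sampling, data collection and analysis are unaffected. I rate it should-fix and no higher, because the unseen information sheet may already state some of the limits.

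**What to change.** - **Section 9, item 8:** promise confidentiality by the research team and de-identified reporting. State that anonymity cannot be guaranteed within focus groups or where a colleague passed on the invitation.
- **Section 8, focus groups:** add a ground rule, agreed at the start of each session, that members keep what they hear confidential.
- **Sections 9, 11.1 and 11.3:** use one wording for quotes, so that item 8 reflects the need for permission and the absence of direct attribution.
- **Section 11.1:** hold the key in an access-controlled store separate from recordings and transcripts.
- **Information sheet:** check that it carries the same limits.

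The cost is revised wording in the protocol, and in the information sheet if needed, plus a second storage location. The drawback is that a more qualified promise may deter a few participants.
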